#### **Objectives of study:**

The general objective of this study is:

- To determine the effectiveness of mobile phone technology (SMS and Phone call reminders) in improving clinic attendance, medication adherence and outcome of treatment among HIV patients on ART.

The Specific objectives include:

1. To determine socio-demographic factors that affect treatment adherence and contribute to treatment default and Lost-to-follow-up (LTFU) among HIV patients on ART.
2. To develop and implement a 'reminder module' (delivered via SMS and telephone calls) to improve clinic attendance and medication adherence among HIV patients on ART.
3. To determine the effectiveness of SMS and telephone call reminders in improving clinic attendance and medication adherence among HIV patients on ART.
4. To determine the effect of medication adherence on the clinical and immunological outcome of HIV patients on ART.

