### Research hypotheses:

**H1:** There is no significant difference in the socio-demographic characteristics of HIV patients who adhere very well to their ART compared to those who do not.

**H2:** The application of mobile phone technology (SMS and phone call reminders) will significantly improve treatment adherence and clinical outcomes of HIV patients on ART, when compared to routine adherence counselling and paper-based appointment scheduling alone.

**H3:** There is a strong and direct relationship between Good adherence to treatment (regular clinic visits and strict medication adherence) and outcome of antiretroviral treatment among HIV patients on ART.

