## RESEARCH APPROACH

### B. Research methodology

**Study Location:** The study will be conducted in Hospital Sungai Buloh, Selangor, Malaysia.

**Study Design:** It will be an experimental (randomized Controlled Trial) study design, single-blinded among newly diagnosed HIV positive patients who are eligible to commence ART from December 2013 to August 2014. Following enrollment and allocation to study arm, baseline adherence, clinical symptoms, CD4 count, viral load, Weight, TB status and Opportunistic infection index will be assessed and measured for the 2 groups, prior to the commencement of ART. The intervention group will receive appointment and medication reminders by text-messaging and telephone calls, in addition to standard care. Based on the Theory of Planned Behaviour Model (Ajzen, 1985), appointment reminders will be sent by Short Text Message (in Malay and English languages) three days prior to each individual client's scheduled appointment and telephone call reminders a day prior to the scheduled clinic appointment visits. Weekly short text messages will also be sent to clients to remind them of taking their medications. The control group will only receive standard care and paper-based appointment during clinic visits. Both groups of clients will be followed up for a period of 6 months on ART. Repeated CD4 count, viral load, Weight, TB status and OI index assessment and measurements will be conducted at 3 and 6 months, respectively to determine treatment outcome. Medication adherence will be measured using structured self-report questionnaires. Clinic visits will be measured through medical records of clinic attendance and clinicians' notes.

**Study Duration:** Recruitment and data collection will be from December 2013 to February 2015.

**Study population:** The study population is all HIV positive clients assessed and found to be eligible for ART commencement at Hospital Sungai Buloh, Selangor

**Inclusion criteria:** Age range of 15 to 65 years eligible to commence ART, able to read text messages and have a mobile phone access.

**Exclusion criteria:** Clients who are previously or currently on ART, foreigners & pregnant patients

**Sampling frame:** It is the list of all HIV positive clients assessed and found to be eligible for ART from December 2013 to August 2014 in Hospital Sungai Buloh, Selangor

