Hence, sample size of 121 per group will be used for the study

**Intervention Protocol:** For the intervention group – a ‘reminder module’ will be developed and delivered via SMS and telephone calls by 2 PLHIV (research assistants). This will include weekly SMS medication reminders, SMS reminders 3 days prior to scheduled clinic appointments and telephone call reminders a day prior to scheduled clinic appointment (in addition to standard care – adherence counseling). To ensure confidentiality, typical medication reminder text messages will include a short slogan in Malay language “Apa khabar” “Ini untuk menberithau anda ubat” meaning “How are you?” “This is to remind you of your medications”. Appointment reminder text message would be “Apa khabar” “Tolong ingat tarikh temu janji lusa” meaning “How are you?” “Remember your appointment day after tomorrow” and telephone conversation would be standardized and short, with the message “Apa khabar” “Tolong ingat tarikh temu janji besok” meaning “How are you?” “Remember your appointment tomorrow”. The control group will receive standard care - routine adherence counseling only. Patients will not be required to provide any responses to the text messages. A call and SMS log will be recorded and kept. Two PLHIV that are stable and have been consistent and adherent to ARV medications for at least 2 years will be recruited as research assistants. Using standard training module developed and validated by a team of experts from Universiti Putra Malaysia and Hospital Sungai Buloh, a two-day onsite training of the research assistants on HIV prevention methods, care and treatment issues and how to respond to common questions related to medication adherence, including medication side effects, when asked by study participants, will be conducted. In addition to sending SMS and making telephone calls to patients, they will also be required to provide counseling support and provide guidance to patients (when required) in filling out medication adherence questionnaires during every clinic visits. Patients in the intervention group will be further divided into 2 sub-groups, each under the supervision of one research assistant, who will be responsible for providing them with counseling and psychosocial support, in addition to the care and management provided by the clinicians and nurses, throughout the duration of the study. Each patient in the intervention group would undergo a minimum of three (during clinic visits at month 1, month 3 and month 6) individual counselling sessions with the research assistants lasting an average of 15 minutes per encounter. An intervention manual containing the training modules and implementation guidelines will be provided to the research assistants as spiral-bound hard copy reference document, to guide their interactions with the patient and assure quality and uniformity in the implementation of the intervention.

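### The intervention arm gets peer counselling and psychosocial support as well as SMS and call reminders, so a difference can be credited to the package but not to reminders alone

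*Protocol*

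**What the plan says.** **The question.** In the protocol's Objectives of study, the general objective is "To determine the effectiveness of mobile phone technology (SMS and Phone call reminders) in improving clinic attendance, medication adherence" and treatment outcome. Specific objective 2 is to build a reminder module sent by SMS and telephone. Specific objective 3 is "To determine the effectiveness of SMS and telephone call reminders in improving clinic attendance and medication adherence among HIV patients on ART". Under Research hypotheses, H2 states: "The application of mobile phone technology (SMS and phone call reminders) will significantly improve treatment adherence and clinical outcomes". Its comparator is given by "when compared to routine adherence counselling and paper-based appointment scheduling alone".

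**The arms in Study Design** (Research methodology). "The intervention group will receive appointment and medication reminders by text-messaging and telephone calls, in addition to standard care". No additional counselling is mentioned there.

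**The arms in Intervention Protocol** (same chapter). The reminder module is defined as weekly medication texts, a text three days before each appointment and a call the day before. The section then adds two items for intervention patients:

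- They are split between two research assistants living with HIV. Each assistant counsels and supports their own group for the whole study, on top of what clinicians and nurses provide.
- They have one-to-one peer sessions. The least number and the timing are fixed by "Each patient in the intervention group would undergo a minimum of three (during clinic visits at month 1, month 3 and month 6", while the provider and the length are fixed by "individual counselling sessions with the research assistants lasting an average of 15 minutes per encounter".

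For the other arm: "The control group will receive standard care - routine adherence counseling only".

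**The concern.** The question and the delivered contrast differ. Objective 3 and H2 attribute the effect to reminders, but the arms also differ in face-to-face peer counselling and psychosocial support. Every intervention patient is assigned both components and no control patient is assigned either, so the two are completely aligned with allocation.

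The added component cannot be set aside as incidental by the protocol's own account. The Background lists weak community support and ineffective adherence counselling among the barriers to adherence. The Literature review names psychosocial support among the correlates of treatment success. It also lists patient education and adherence case management as kinds of intervention separate from reminder devices. The reminder calls, by contrast, are meant to be short and scripted.

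What is at stake is the meaning of the main result. Adherence and clinic attendance, the two primary outcomes, are the outcomes named in objective 3. If the trial is positive and H2 is accepted as worded, the report would credit SMS and calls with an effect that may belong partly or wholly to the peer sessions. A service that then introduced reminders alone would be relying on evidence the trial did not produce.

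**Working it through.** The point turns mainly on setting the arm descriptions side by side.

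| Component | Intervention arm | Control arm |
|---|---|---|
| Standard care with routine adherence counselling | yes | yes |
| SMS and call reminders | yes | no |
| Individual peer sessions, months 1, 3 and 6, average 15 minutes | yes, at least 3 | none scheduled |
| Continuing peer psychosocial support | yes, amount not stated | none assigned |

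**1. Amount of extra counselling.** Scheduled minimum: 3 sessions x 15 minutes = 45 minutes. The primary adherence outcome counts pills missed in the 30 days before the month 6 assessment, and attendance is judged at six months. A session held during the month 6 visit can change neither the preceding 30 days nor whether that visit was attended. The month 1 and month 3 sessions come before the window: 2 x 15 = 30 minutes. The continuing support comes on top and cannot be quantified from the protocol.

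**2. What the comparison identifies.** Write R for the effect of reminders, C for the effect of peer counselling and support, and I for any interaction. The expected difference between arms is

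D = R + C + I.

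The trial yields one randomised contrast per outcome, D, for three unknowns. Even with I = 0, R = D - C. If C lies anywhere between 0 and D, R lies anywhere between D and 0. Separating them needs patients who get one component without the other, and the 1:1 two-arm design has none. Covariate adjustment does not help. Using the number of sessions or messages actually received would be a non-randomised comparison within one arm.

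**3. Illustration with the protocol's planning figures.** The stated sample size reproduces when the difference is squared: 2 x 132² x (1.96 + 0.842)² / 50² = 109.4, rounded up to 110 per arm. Assume, for illustration only, that the 50-cell CD4 difference is the package effect D. The standard error is 132 x √(2/110) = 17.8, and 50 / 17.8 = 2.81. Power is Φ(2.81 - 1.96) = Φ(0.85), about 80%. This depends on D alone. The trial would be significant about 80% of the time if reminders produced all 50 cells, and equally often if they produced none and counselling produced all 50. CD4 is a secondary outcome, so this shows the logic and is not an estimate of the error in the primary result.

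**The case against.** - **Testing a package is legitimate.** This stands. A reader might infer that the trial is biased or cannot give a useful answer. The documents do not support that: the package effect is validly estimable from the randomised arms. What is wrong is that no objective or hypothesis names the package.
- **Controls are counselled too.** True, but routine counselling is standard care in both arms and cancels. Its length is not stated, so the relative increase in counselling is unknown. The zero for controls refers only to scheduled peer sessions. The Intervention Protocol also has the assistants give counselling support and questionnaire guidance to patients at every visit, without clearly restricting this to one arm. Some contact with controls is therefore not excluded. That might shrink the contrast but would not separate its components.
- **45 minutes overstates the dose.** This stands for the primary outcomes, where about 30 scheduled minutes are relevant.
- **The protocol does not promise to scale up phone reminders.** This also stands. A reader might infer that Significance of research foresees a recommendation specific to mobile phones. It speaks only of the intervention as a strategy, and Expected outcomes compares only intervention and control groups. Both fit the package as they are. The reminder-only wording is in the objectives, H2 and Study Design.
- **An analysis plan could deal with it.** It could not, because the components do not vary independently of arm. It could only restate what is being estimated.

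**Conclusion.** The objectives, H2 and Study Design contradict the Intervention Protocol on what is being tested. Followed as written, the plan would lead to a conclusion about SMS and phone reminders that the data cannot support. The comparison supports a conclusion about reminders together with peer counselling and psychosocial support.

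The unreported part of the contrast is at least 45 scheduled minutes of one-to-one peer counselling per intervention patient, about 30 of which can influence the primary outcomes, plus support of unstated amount. The share of any effect due to reminders is not identifiable. It would go too far to say that a positive result would in fact come from the counselling, since the documents give no evidence on the split either way.

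This rests on two readings: that the sessions and support are delivered as the Intervention Protocol describes, and that controls do not receive equivalent peer contact, which is the plain sense of their description. Limitations lists three items, and this is not among them.

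**What to change.** Reconcile the Objectives of study, Research hypotheses and Study Design with the Intervention Protocol:

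1. Restate the general objective, specific objectives 2 and 3, H2 and the Study Design description of the intervention arm so that each names a package of SMS and call reminders plus peer counselling and psychosocial support.
2. Limit the conclusion, and any recommendation to scale up, to that package.
3. Add to Limitations that the effect of reminders alone cannot be separated from that of peer counselling and support.

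Significance of research and Expected outcomes can stay as they are. The cost is a narrower claim: the trial no longer says whether reminders work by themselves. Randomisation, conduct, sample size and data collection are unchanged. Giving both arms the same peer contact would keep the reminder question, but that changes conduct and is not needed to make the protocol consistent.

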
**Data collection:** Research data will be collected using the below plan:

- **How:** 2 types (Primary and Secondary) of data will be collected from 3 main sources;

(a) Hospital medical records – Patients’ socio-demographic and clinic attendance data will be collected from hospital records; pharmacy records will be utilized for measuring adherence to drug refill appointments, while clinicians’ notes will be assessed for clinical information regarding weight, TB status, and OI index of clients (through standardized OI monitoring forms). Laboratory records will be accessed for baseline and follow-up CD4 count and viral load test results.

(b) Structured questionnaire and standardized medication adherence monitoring forms would be used to collect information from clients’ medication adherence self-reports during interaction with clinician/nurses/pharmacists at every scheduled clinic visit/appointment.

- **Who and When:** Socio-demographic (at enrolment) and clinic visit information (at every visit) will be collected by clinic medical record officers, laboratory information by laboratory scientists (at baseline, Months 3 and 6) and clinical and medication adherence information will be collected by clinicians/nurses/pharmacists at every client visit.

A log book on phone calls and text messages will also be recorded.

- **Duration:** Data will be collected over a 13 months period.
- **Questionnaire:** The Adult AIDS Clinical Trial Group (AACTG) adherence questionnaires (Chesney, M.A. et al, 2000) will be adapted with slight modifications, for the purpose of this study. Specialized questionnaires will be used at baseline and follow up. The questionnaire will be pre-tested on a population not included in the sample for validity and reliability.

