| Clinical (Wt, TB & OI status)                   | Clinician's notes       | Clinicians/nurses/adherence counsellors          | Every visit                                       |
| Immunological (CD4)
Virological (viral load) | Laboratory records      | Laboratory scientists                            | Baseline & 6mths                                  |
| Medication adherence                            | Adherence questionnaire | Research assistants/nurses/adherence counsellors | Baseline, then every visit (particularly 3&6mths) |

- **Data Storage:** All data generated from this study will be stored for a maximum of 3 years after the completion of the study, after which they will be destroyed. However, during this period they will remain joint intellectual property of Universiti Putra Malaysia and Hospital Sungai Buloh.

**Primary Outcomes:** The first primary outcome is (improved) patient adherence to ART at six months. This is assessed by self-report using a standardized questionnaire of the number of pills missed in the last 30 days and calculating percent adherence based on the expected number of doses taken and/or number of missed doses. Percent adherence will be analyzed as continuous variable and polytomous variable. Subjects will be considered as "Good adherence" when they achieve an optimal adherence cut of >95% of medications taken as directed with <3 missed doses in the last 30 days period. "Fair adherence" will be considered as 80-95% of medications taken as directed with 3-8 missed doses in the last 30 days period, while "Poor adherence" will be considered as <80% of medications taken as directed with >8 missed doses in the last 30 days period. Medication adherence will be assessed at each follow-up visit, particularly at months 3 and 6. The six month scheduled follow-up is the primary analysis but the three month assessment will allow for evaluating trends but is not the primary outcome.

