The other secondary outcome is (improved) immunologic status/response of patients at six months. This will be assessed based on records of two (2) laboratory measurements – CD4 T cell count and viral load. Patients' CD4 count results at six months will be assessed and compared with baseline values to determine if there's a consistent increase (or otherwise) as expected with strict medication adherence. If patients are adherent to ART regimens, absorb the drugs normally, and if their virus is not resistant to the ART drugs in the regimen, it is expected that their CD4 count should increase from baseline levels by at least 50 cells per microliter of blood within 6-12 months of initiating treatment. CD4 count value at six month scheduled follow-up is the primary analysis.

Similarly, plasma HIV RNA load results at six months will be assessed and compared with baseline levels to determine if there is a significant suppression at six months. If patients are adherent to ART regimens, absorb the drugs normally, and if their virus is not resistant to the ART drugs in the regimen, it is expected that their plasma HIV load should be suppressed to undetectable levels (<400 copies/ml) by six months and remain suppressed thereafter. Analysis of "suppressed" (<400 copies/ml) versus "failure to suppress" (>400 copies/ml) at six months as a dichotomous variable is the primary analysis.

**Data analysis:** Data collected will be collated, checked, cleaned, entered into and analyzed using Statistical Package for Social Sciences software (SPSS) version 21 and AMOS software. Parametric tests (T-test, repeated measures ANOVA) and non-parametric tests will be conducted on the data. P value for test of significance of results will be set at 0.05, alpha level (Type 1 error) at 0.05 (Confidence Interval of 95%), Power at 80% to detect an impact of 15% in the fraction of patients with adherence of at least 90% (assuming a no intervention median adherence level of 90%) using a two-tailed test, Z=1.96, and strength by effect size analysis. Analysis will be by intention-to-treat and complete case analysis.

| Independent variable                                                    | Dependent variable                                                           | Type of analysis                                                           |

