|-------------------------------------------------------------------------|------------------------------------------------------------------------------|----------------------------------------------------------------------------|
| Categorical (socio-demographic, behavioural & adherence factors) | Continuous (Wt, CD4, viral load)                                      | T-test, Repeated Measures ANOVA                                     |
| Categorical & Continuous (All IVs)                           | Categorical (adherence level, TB status, OI index, viral suppression) | Multivariate/Multinomial Logistic Regression Model                  |
| Categorical (All IVs converted to categorical)                   | Categorical (All DVs converted to categorical)                        | -Structural Equation Modelling
-Chi-square (sub-group analysis) |

**Limitations:** (1) Self-report of adherence – exaggeration of true adherence (Pharmacy refill records, CD4 count and viral load will provide a means of validating the responses)

(2) Pill count will not be used

(3) Structured questionnaires may not elicit in-depth information

**Ethical considerations:** The study and materials will be presented to the UPM Ethics approval committee and the Malaysian Ministry of Health's Institutional Review and Ethics Committee for review and approval. Thereafter, permission will be sought from the Medical Director of the hospital in writing to use their clients. The researcher will work in collaboration with attending clinicians, nurses and pharmacists in identification and monitoring of the clients.

**Expected outcomes:** The expected outcomes of this research include:

1. A significant difference in treatment adherence (medication adherence and regular, scheduled clinic attendance) is expected in the intervention group compared to the control group.
2. Better clinical outcome in the intervention group compared to the control group.
3. Socio-demographic, psychosocial and other risk factors that determine differences in treatment adherence between the intervention and control groups will be identified.
4. Provide baseline information on the effectiveness of current standard of care (routine adherence counselling) on treatment adherence and clinical outcomes.

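### CD4 and viral load are scheduled at month 3 in two places but not in the data-collection table; the month-6 outcomes are unaffected, but the schedule needs reconciling

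*Protocol*

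**What the plan says.** All statements are in the Protocol, section B (Research methodology).

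- **Study Design:** "Repeated CD4 count, viral load, Weight, TB status and OI index assessment and measurements will be conducted at 3 and 6 months, respectively".
- **Data collection, Who and When:** "laboratory information by laboratory scientists (at baseline, Months 3 and 6".
- **Data-collection table, CD4 and viral load row:** "Baseline & 6mths".
- **Secondary Outcomes, laboratory part:** for CD4, "CD4 count value at six month scheduled follow-up is the primary analysis"; for viral load, suppression versus failure to suppress, "at six months as a dichotomous variable is the primary analysis". Both are compared with baseline, and no month-3 laboratory assessment is named.
- **Data analysis:** "Parametric tests (T-test, repeated measures ANOVA) and non-parametric tests will be conducted on the data". The table below that paragraph puts weight, CD4 and viral load together as continuous dependent variables under "T-test, Repeated Measures ANOVA". Neither the paragraph nor the table lists the time points.

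**The concern.** Two statements give three laboratory time points (baseline, month 3, month 6) and one gives two (baseline, month 6). The conflicting statement is in the table that sets out source, responsible person and time of collection, which is a natural working reference for site staff. A site that followed it would have no reason to request month-3 tests.

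The timing of blood tests belongs to the protocol. A later statistical analysis plan can choose the model, but it cannot supply results from tests that were never done. The choice also decides what the listed repeated measures ANOVA of CD4 and viral load can show: a course over three points, or only a before-and-after comparison.

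**Working it through.** **1. Is the conflict genuine?** The word respectively in the Study Design sentence is loose and could be misread. The Who and When item has only one reading: laboratory data at baseline, month 3 and month 6. The table entry is in the row for CD4 and viral load. The next row of the same table, on medication adherence, does name months 3 and 6, so the author wrote month 3 there where it was meant. Damage in text extraction is therefore an unlikely explanation.

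**2. Do the defined outcomes need month 3?** No. The laboratory outcomes are secondary and set at month 6 against baseline. For adherence, clinic attendance and clinical status, the outcome text adds a three-month look at trends. For CD4 and viral load it does not.

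**3. Does the sample size depend on month 3?** Inputs from the Sample size paragraph: SD 132, difference 550 − 500 = 50, Z values 1.96 and 0.842.

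n = 2 × SD² × (1.96 + 0.842)² / difference² = 2 × 132² × 2.802² / 50² = 109.4, rounded up to 110 per group.

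This reproduces the protocol's 110; power at 110 per group is 80.2%. (The printed line shows the difference unsquared, which would give 5,472; the stated 110 follows from the squared form.) The 50-cell difference is described as the increase expected within 6 months. No month-3 quantity enters.

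**4. What does the repeated measures ANOVA become with two time points?** With values Y0 and Y6 in each patient, the group-by-time interaction is a single contrast:

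(mean of Y6 − Y0 in one group) − (mean of Y6 − Y0 in the other).

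The F test of that contrast is the square of the two-sample t statistic on change from baseline, with the same p-value. With three time points the interaction has two degrees of freedom and the month-3 course can be described. The test on two points is valid, but it gives no month-3 trend.

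**5. How many patients could have a month-3 value but no month-6 value?** The protocol does not say when losses occur, so this needs an assumption. With a constant hazard and a fraction L lost by month 6, the fraction lost between months 3 and 6 is √(1 − L) − (1 − L).

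- L = 10% (the stated attrition): √0.90 − 0.90 = 0.9487 − 0.9000 = 0.0487; × 242 = 11.8.
- L = 11/121 = 9.1% (the loss implied by inflating 110 to 121): √0.9091 − 0.9091 = 0.9535 − 0.9091 = 0.0444; × 242 = 10.7.

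That is about 11 to 12 patients. If all losses came before month 3 the number would be 0. If all came after month 3 it would be 22 (9.1% of 242) to 24 (10% of 242). These patients add information only under a model that uses incomplete cases. A classical repeated measures ANOVA, or the complete case analysis that the Data analysis paragraph names alongside intention-to-treat, would drop them even if their month-3 result existed.

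**The case against.** The strongest reply is that nothing defined in the protocol needs month-3 laboratory values. The table agrees with the outcome definitions, which name only baseline and month 6. The row of the analysis table that lists repeated measures ANOVA also contains weight, which is recorded at every visit, so the method has a use there under either schedule. That row's independent variables are socio-demographic, behavioural and adherence factors; study arm is not named. A repeated measures ANOVA on two points is also sound and suits a comparison of month 6 with baseline.

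All of this stands, and it limits how much weight the point can bear. It does not remove the conflict: two explicit statements still schedule tests that the table leaves out.

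A reader might go further and infer three things that the documents do not support:

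- **That the planned analysis will lose month-3 data it requires.** No statement says that month-3 laboratory values enter the repeated measures ANOVA. That is only a reasonable inference from reading the schedule and the analysis table together.
- **That about 12 patients are lost to the analysis.** That number rests on an assumed timing of loss, and the methods named would not use those patients.
- **That the values will certainly go uncollected and be unrecoverable.** The Who and When item also assigns the laboratory staff and includes month 3. Results are taken from laboratory records, so a test that was done could still be retrieved; only a test not done is lost. The documents do not show which would happen.

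**Conclusion.** The protocol contradicts itself on when CD4 and viral load are measured: three time points in two places, two in the data-collection table. The effect is limited to two matters: whether month-3 laboratory values are obtained at all, and whether the listed repeated measures ANOVA of CD4 and viral load has three time points or two. The month-6 comparisons and the 110 per group are untouched.

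No numerical loss to the plan as written is shown. The 11 to 12 patients depend on constant-hazard loss and on a model that the protocol does not state. This is a minor consistency correction to the timing of secondary outcomes. It is worth making because the document cannot be followed as written and a month-3 test not done at the time cannot be done later.

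**What to change.** Reconcile the Study Design paragraph, the Who and When item and the CD4/viral load row of the table. Which schedule applies is for the sponsor to decide.

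- **If month 3 stands:** add it to the table entry, and state that baseline, month 3 and month 6 enter a repeated-measures model that keeps patients with incomplete data, such as a linear mixed model. The text change is one table entry and one sentence. If these tests are not already being done, the real cost is up to 242 additional CD4 and 242 additional viral load tests; the budget detail is in an appendix that is not available here.
- **If month 3 is dropped:** delete it for CD4 and viral load (not for weight, TB status or the opportunistic infection index) from the Study Design paragraph and the Who and When item. Analyse month-6 CD4 adjusted for baseline CD4, which is already collected, and keep viral load as month-6 suppression, as Secondary Outcomes has it. The cost is two text edits and one sentence in Data analysis. The baseline adjustment is a recommendation for precision; the two-point ANOVA would remain valid.

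Under either choice, Data analysis should list the time points used for CD4 and viral load.
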